### Statistical analysis

#### Baseline comparison

Examine potential baseline differences between the three groups. Chi-square test was used to measure gender, education, and pathological characteristics (intracerebral hemorrhage or cerebral infarction). One-way ANOVA was used to analyze pre-intervention assessment results and information such as age. Baseline comparisons were used to detect potential differences between the intervention and sham-EA group, ensuring that there were no differences between the three groups.

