**Methods:**

After assessing their eligibility, 66 patients with stroke will be enrolled from two Chinese medicine hospitals and randomly divided into theta frequency EA group, gamma frequency EA group, and sham-EA group according to the ratio of 1:1:1. All patients will receive 20 sessions of EA procedures for 4 weeks. Patients in three groups will receive EA at two same acupoints in the head: Baihui (GV20) and Shenting (GV24). The frequency of the three groups of EA is set as follows: 6 Hz (theta-EA group), 40 Hz (gamma-EA group), and no current through the electrodes (sham EA). Patients and assessors will be blinded throughout the entire study. The primary outcome is the performance accuracy of 1-back task which is a frequently used measure of WM in cognitive neuroscience research contexts. Secondary outcome measures will include the response time of 1-back task, the Rivermead Behavioral Memory Test, Trail Making Test, Loewenstein Occupational Therapy Cognitive Assessment Scale, modified Barthel Index, and electroencephalogram (EEG) signals during 1-back tasks. A blinding index will be assessed. Data will be statistically analyzed by one-way ANOVA, at 5% of significance level.

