### Randomization and allocation

For randomization, to reduce the chance of bias and confusion and increase the probability of meeting statistical analysis assumptions, a restricted randomization with a random block size between 3 and 6 will be used (the exact size is determined by an external agency) [28]. Two centers will both receive a computer-generated random list from third-party partners (MATLAB 2012b, Mathworks Inc., Natick, MA, USA) which will not participate in this research. Envelopes with sequential numbers are opaque and sealed and will be distributed to each test center by a third-party agency that is not part of the research team. Before the first treatment and after the treatment is completed, the therapist will be notified to perform a baseline and post-treatment evaluation of the patient.

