### Sample size calculation

The primary endpoint was the difference of accuracy (d`) scores respectively at baseline and endpoint between the three groups (gamma-EA group, theta-EA group, and sham-EA group) in the 1-back test for patients with post-stroke. Since we did not have enough previous research as the basis for our estimated sample size, we chose the data collected in the previous pre-experiment to calculate the sample size required for this experiment. The null hypothesis is that *μ*_*i*_ = *μ*_*j*_ = *μ*_*t*_, while the alternative hypothesis is *μ*_*i*_ ≠ *μ*_*j*_ ≠ *μ*_*t*_, where *μ* is the mean difference and *i*, *j*, and *t* denote the sham-EA, gamma-EA, theta-EA group, respectively. Our pre-experimental results of 1-back accuracy (d`) scores show that after treatment, the d` values of the gamma-EA group (2.48 ± 0.32) and the theta-EA group (2.02 ± 0.53) are improved compared with the sham-EA group (1.88 ± 0.60). Using the sample size calculation formula for comparing the average of multiple independent samples in the parallel design, under the assumptions of α of 0.05 and (1-β) of 0.8, a sample size of 18 per group has been calculated. Considering a 20% dropout rate, a total of 66 patients will be enrolled in the trial (22 per group). The specific calculation formula is as follows [38]: *n* = λ/Δ

$$ \Delta =\frac{1}{\sigma^2}\sum \limits_{i=1}^K{\left({\mu}_i-\overline{\mu}\right)}^2\kern0.5em \overline{\mu}=\frac{1}{k}\sum \limits_{j=1}^k{\mu}_j $$

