#### The efficacy analysis will use an intention-to-treat analysis

The results of 1-back evaluation are based on the accuracy and response time as the observation indicators. The evaluation results of RBMT, TMT, LOTCA, and MBI are summarized according to the calculation rules of each scale. The results of each of the above assessments are expressed as mean ± SD. The statistical method uses analysis of variance (assuming a normal distribution) and using Kruskal-Wallis (non-parametric test) to test if it does not meet the normal distribution. The significance level was 95% (*p* values alpha < 0.05 on both sides). If the data is missed, the last observation carried forward method will be applied.

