#### Specific calculation schemes for the RT value and accuracy of the 1-back paradigm [39]

The RT value in this study is selected for analysis by the RT value (RT-hit), which is the most common method to evaluate the response. Accuracy is represented by the value of d`. The specific formula is as follows: *d* = *Z*_Hit_ − *Z*_FA_. Among them, *Z*_Hit_ and *Z*_FA_ are converted to *Z* values from the hit rate and false alarm rate according to the POZ conversion table. After calculating the *d* value and RT value of each subject, data were imported into SPASS, and one-way ANOVA was used to compare the differences between the three groups before and after the intervention.

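### The primary d' comparison is a one-way ANOVA without baseline d' or centre, and baseline tests are wrongly said to ensure balance: a valid test, but less precise than the collected data allow

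*Protocol article*

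**What the plan says.** Three places in the protocol article name the efficacy test.

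- Abstract, Methods: "Data will be statistically analyzed by one-way ANOVA, at 5% of significance level".
- Statistical analysis, the section on the intention-to-treat efficacy analysis: analysis of variance, with Kruskal-Wallis when the data are not normal.
- The section on the RT value and accuracy of the 1-back paradigm: "one-way ANOVA was used to compare the differences between the three groups before and after the intervention".

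None of these carries a covariate. The section on the new BI closes by stating that no additional analyses are planned.

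Under Baseline comparison, chi-square tests are planned for categorical characteristics, and for the rest: "One-way ANOVA was used to analyze pre-intervention assessment results and information such as age". The purpose given is: "Baseline comparisons were used to detect potential differences between the intervention and sham-EA group, ensuring that there were no differences between the three groups". No action is described if a difference is found.

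Two design facts bear on the model. Every patient is evaluated the day before the intervention starts (Study design), so baseline d' exists for all. And under Randomization and allocation: "Two centers will both receive a computer-generated random list from third-party partners".

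The endpoint wording is open. Sample size calculation says: "The primary endpoint was the difference of accuracy (d`) scores respectively at baseline and endpoint between the three groups". This can mean a comparison at each time point. The same section calls μ a mean difference, which allows a change score, but it sizes the trial on post-treatment means.

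**The concern.** A one-way ANOVA has arm as its only factor, so baseline d' cannot enter as a covariate and centre cannot enter at all. Baseline d' is likely to be the strongest available predictor of post-treatment d', and it is already collected. Leaving it out discards precision in a trial that its own Limitation section calls small.

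The sentence about ensuring no differences adds to this, because it suggests that a non-significant baseline test removes the need to adjust. It does not. Under correct randomisation any baseline difference is due to chance, and about 5% of such tests will be significant anyway. A non-significant result does not show that the arms are alike in this sample. What remains carries into a post-treatment comparison with the same sign, and into a change comparison with the opposite sign through regression to the mean.

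**Working it through.** **Inputs.** From Sample size calculation: post-treatment d' of 2.48 (SD 0.32) for gamma, 2.02 (SD 0.53) for theta and 1.88 (SD 0.60) for sham; α 0.05; power 0.80; 18 per group, raised to 22 for dropout. The article does not say which σ it used and gives no baseline-to-endpoint correlation ρ. I assume ρ from 0.2 to 0.7, equal SDs at both times and equal expected baseline means.

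**Reproducing 18 per group.** The mean of the three means is 2.127. The sum of squared deviations is 0.353² + 0.107² + 0.247² = 0.197. For 2 degrees of freedom and 80% power, λ = 9.635.

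- σ = 0.60 (largest pilot SD): Δ = 0.197/0.36 = 0.547; n = 9.635/0.547 = 17.6, so 18. This matches.
- Pooled σ = √[(0.32² + 0.53² + 0.60²)/3] = 0.498: Δ = 0.795; n = 12.1, so 13. This does not match.

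I therefore take σ = 0.60 as the main case.

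**Residual variance of each analysis.**

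- Post-treatment ANOVA: σ²
- Change-score ANOVA: 2σ²(1 − ρ)
- ANCOVA: σ²(1 − ρ²)

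The ANCOVA variance is (1 − ρ²) times the first and (1 + ρ)/2 times the second. Both ratios are below 1 for any ρ between 0 and 1, so ANCOVA is more efficient on either reading of the endpoint.

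**Power at 18 per arm.** Non-central F with non-centrality 18 × 0.197/(residual variance); 51 error degrees of freedom for ANOVA, 49 for ANCOVA with baseline and centre.

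| ρ (assumed) | Post ANOVA | Change ANOVA | ANCOVA |
|---|---|---|---|
| 0.2 | 0.78 | 0.57 | 0.80 |
| 0.3 | 0.78 | 0.63 | 0.82 |
| 0.4 | 0.78 | 0.70 | 0.85 |
| 0.5 | 0.78 | 0.78 | 0.89 |
| 0.7 | 0.78 | 0.95 | 0.98 |

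With the pooled SD of 0.498, post-treatment ANOVA already has 0.92, against 0.93, 0.94 and 0.97 for ANCOVA at ρ = 0.2, 0.3 and 0.5. These ANCOVA figures include no gain from centre, because no centre variance is given.

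**Type I error, overall and given imbalance.** For each ρ, 40,000 null trials were simulated with 22 per arm. Over all trials the error was about 5% for all three methods. Among trials whose three-group baseline test gave p between 0.05 and 0.20, which the plan would read as no difference, it was:

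| ρ (assumed) | Post ANOVA | Change ANOVA | ANCOVA (baseline only) |
|---|---|---|---|
| 0.3 | 6.7% | 10.5% | 5.2% |
| 0.5 | 8.6% | 8.6% | 5.0% |
| 0.7 | 11.6% | 8.2% | 5.3% |

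So a non-significant baseline test does not protect the efficacy test.

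**The case against.** The strongest reply is that nothing is broken. Randomisation makes the unadjusted ANOVA valid, and the sample-size formula, which compares several independent means, was built for that test. This stands, and it limits the point to precision and to error conditional on the observed imbalance.

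Four stronger readings are tempting, and the documents do not support them.

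- **Chance imbalance biases the result.** At 22 per arm the baseline gap between two arms has standard error 0.60 × √(2/22) = 0.18. With ρ = 0.6, one standard error shifts the post-treatment contrast by about 0.11, which looks large beside the pilot theta-sham difference of 2.02 − 1.88 = 0.14. But the unadjusted post-treatment contrast also has standard error 0.18, and the shift is already part of it (0.6² = 36% of its variance).
- **The baseline test would miss most real gaps.** A two-arm t-test at 22 per arm has about 37% power for a half-SD gap. That is power against a population difference, which randomisation sets to zero. The sound objection is that the test answers the wrong question.
- **The plan ignores baseline.** This is strictly true only if post-treatment values are analysed. With change scores, baseline is subtracted, though not adjusted for.
- **Omitting centre invalidates the intervals.** The article says that both centres receive a list; it does not call the randomisation stratified. Where centre matters, leaving it out usually makes intervals too wide, which is conservative. The size cannot be computed from the documents.

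It can also be said that covariates are commonly left to a statistical analysis plan. Here, though, the article names the one-way test and states what the baseline tests achieve, so both are open to comment.

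**Conclusion.** The point holds as one of efficiency and wording. The protocol fixes a one-way ANOVA with no baseline or centre term, and its claim that baseline tests ensure equality is wrong. The planned test remains valid on average over randomisation.

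The direction of the gain from ANCOVA is certain for any ρ between 0 and 1; its size is not. At σ = 0.60 it ranges from negligible against post-treatment ANOVA (0.80 against 0.78 at ρ = 0.2) to substantial (0.98 against 0.78 at ρ = 0.7). Against change-score ANOVA the order reverses: large at low ρ (0.80 against 0.57) and small at high ρ (0.98 against 0.95). With the pooled SD there is less to gain. The pilot behind these SDs had nine patients in all (Outcome measurements selection), so the absolute power figures are rough. The case for the centre term rests on the lists supplied to each centre, not on a computed benefit.

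**What to change.** State the primary analysis as an ANCOVA of post-treatment d' on arm, baseline d' and centre, reporting adjusted differences from sham with 95% confidence intervals. This also settles whether post-treatment values or change are analysed.

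Report baseline data descriptively by arm. Delete the baseline significance tests and the sentence claiming that they ensure no differences.

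How to handle clearly non-normal residuals, in place of the switch to Kruskal-Wallis, and whether to use the same model for the secondary scales are choices for the trial team; this point does not depend on them.

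The cost is two model degrees of freedom (error degrees of freedom fall from 51 to 49 at 18 per arm) and a protocol amendment. No new patients, visits or data are needed. Recruitment is ongoing under version 1, and the steering committee approves major protocol changes, so the amendment should go through that route before unblinding. Adjustment chosen after an imbalance has been seen would be data-driven.

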#### The efficacy analysis will use an intention-to-treat analysis

The results of 1-back evaluation are based on the accuracy and response time as the observation indicators. The evaluation results of RBMT, TMT, LOTCA, and MBI are summarized according to the calculation rules of each scale. The results of each of the above assessments are expressed as mean ± SD. The statistical method uses analysis of variance (assuming a normal distribution) and using Kruskal-Wallis (non-parametric test) to test if it does not meet the normal distribution. The significance level was 95% (*p* values alpha < 0.05 on both sides). If the data is missed, the last observation carried forward method will be applied.

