### Study design

This study is a two-center, randomized, sham-controlled, blinded patient and evaluator, parallel clinical trial. Our study will show if it is feasible to arrange patients randomly in EA trials of WM after stroke. The results of the study will be used to sample size calculation to provide a basis for subsequent research.

Sixty-six post-stroke patients will be recruited to participate in the trial. Before the experiment begins, the doctor will provide specific information about the trial to patients both orally and in writing. All patients will voluntarily sign an informed consent provided by the attending doctor. The informed consent was approved by the ethics committee before the formal experiment begins. All patients will be screened according to eligibility criteria. Sixty-six post-stroke patients will be randomly divided into theta-EA group, gamma-EA group, and sham-EA group according to the ratio of 1:1:1. The EA treatment and evaluation did not perform simultaneously. The evaluation will be performed the day before the intervention. The second evaluation is at least 2 h after the last intervention. All patients will receive an intervention that lasts for 4 weeks (30 min a day, 5 days a week, Monday to Friday).

Considering that the focus of this experiment is to explore the effects of EA at different frequencies on WM, patients in three groups will receive EA at two same acupoints in the head: Baihui (GV20) and Shenting (GV24). The frequency of the three groups of EA is selected as follows: 6 Hz (theta-EA), 40 Hz (gamma-EA), and no current through the electrodes (sham EA). The overall schematic diagram and schedule for the study are respectively shown in Figs. 1 and 2.

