### Blinding

To minimize deviations and disturbances caused by other factors, the acupuncturist will not give the patient any information about the treatment. In this study, the interventions that patients received in three groups will keep as consistent as possible except for different frequencies. Even needles’ position, angle, depth, and acupuncture technique that patients received will be kept completely consistent. Visually, the sham-EA group looks the same as the two observation groups. The electrodes will be connected to the needle body, and the EA instrument will also be turned on and modulated with the parameters. During the three groups of treatments, the EA instrument was placed on the back of the patient to ensure that the patient could not see the parameters of the stimulation. The specific stimulation scheme of sham EA will be introduced in the chapter of fake EA. The above scheme ensures that patients do not know what kind of intervention they are receiving. At the same time, assessors are not involved in the treatment to ensure the completion of the blind method. At the end of the study, patients and assessors will be asked to try to infer which group they think they belong to. Judgment results are calculated through new blindness index (BI) [29] to assess the success or failure of blinding. Unblinding should be determined on a case-by-case basis and considered only in a critical medical emergency. If unblinding happen, the subject will be terminated from the trial immediately, and the investigator will record the reason for the termination in the CRF. All data will be retrieved with the CRF after the trial, so as to analyze the reason, scope, and time of unblinding to evaluate the efficacy and safety of the study.

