#### Dropout criteria

Patients will be discontinuing interventions if they meet one or more following criteria: (a) mistakes/acceptances (subjects who were mistakenly included); (b) subjects have poor compliance and have not been treated as prescribed, for example, subjects who cannot cooperate with researchers or subjects who are unable to remain quiet and stay still or subjects who cannot come to treatment on time; (c) incomplete medical record data that affects the evaluation of efficacy; (d) subjects withdraw on their own; (e) subjects have adverse events (including recurrence of stroke or cerebral hemorrhage, stuck needles, bent needles, hematoma, pain, and metal allergy); (f) the subject’s disease has worsened severely, or some comorbidities, complications, and special physiological changes have occurred (which is unknown adverse events that we may encounter during the study); and (g) the researcher believes that the subject is not suitable to continue participating in this study.

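### With one baseline and one post-treatment assessment, LOCF can only carry the baseline forward, so a patient without the post-treatment 1-back is scored as exactly zero change

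*Protocol article*

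**What the plan says.** The subsection of Statistical analysis on efficacy is headed "The efficacy analysis will use an intention-to-treat analysis". It covers 1-back accuracy and response time, RBMT, TMT, LOTCA and MBI, and ends with the missing-data rule: "If the data is missed, the last observation carried forward method will be applied". No other method for missing outcomes is named.

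Study design fixes two assessments. For the first, "The evaluation will be performed the day before the intervention"; for the other, "The second evaluation is at least 2 h after the last intervention". Randomization and allocation agrees: "the therapist will be notified to perform a baseline and post-treatment evaluation of the patient". No interim assessment is described.

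Sample size calculation arrives at 18 patients per group and raises this to 22 (66 in total) for 20% dropout.

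Three passages bear on who will lack the second assessment:
- Blinding: "If unblinding happen, the subject will be terminated from the trial immediately".
- Dropout criteria: "Patients will be discontinuing interventions if they meet one or more following criteria". The list includes adverse events, worsening and poor compliance.
- Data collection methods and management promises to gather whatever data it can from participants who discontinue or deviate. It does not say that this includes the post-treatment 1-back.

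**The concern.** LOCF presupposes a series of post-baseline visits, and here there is only one. When that one is missing, the last observation is the pre-treatment score. The rule becomes baseline carried forward, and the patient contributes a known change of zero.

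Zero is not a neutral guess. All arms receive conventional rehabilitation and repeat the same task, so scores may rise in every arm, sham included. A patient who stops because of worsening may have fallen below baseline. At stake are the size of the estimated effect and the power of a small trial. If missingness is unequal between arms, the error rate of the primary test is at stake too.

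**Working it through.** **Inputs from the protocol.** Post-treatment pilot d': gamma 2.48 (SD 0.32), theta 2.02 (SD 0.53), sham 1.88 (SD 0.60). Alpha 0.05, power 0.80, 22 per group, 20% dropout, one-way ANOVA.

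**Inputs assumed, because the protocol gives neither.** Baseline mean d' b from 1.2 to 1.88, and baseline-to-post correlation 0.5 (range 0.3 to 0.7). SD is taken as 0.60 at both visits.

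**1. The plan's own figure.** The formula is n = λ/Δ.
- The mean of the three pilot values is 2.127, so Σ(μi − mean)² = 0.1971.
- With σ = 0.60, the largest pilot SD, Δ = 0.1971/0.36 = 0.547.
- With λ = 9.635 (2 df, alpha 0.05, power 0.80), n = 9.635/0.547 = 17.6, hence 18. Then 18 × 1.2 = 21.6, hence 22.

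The stated size is reproduced. After 20% dropout, 22 × 0.8 = 17.6 completers per group remain. Their power is 80% by this formula and 77% by the exact F distribution.

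**2. Effect on the estimate, equal missingness.** With a fraction m missing at random, the expected LOCF mean of an arm is (1 − m)μ + m·b. With equal m and a common baseline, b cancels: gamma minus sham = 0.8 × (2.48 − 1.88) = 0.8 × 0.60 = 0.48.

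**3. Effect on power, equal 20% missingness.** The signal Σ(μi − mean)² becomes 0.64 × 0.1971 = 0.126. The within-arm variance also changes, where δ is the arm's mean gain over baseline:
- Post-treatment values: 0.36 + 0.2 × 0.8 × δ². Mixing baseline and post scores adds variance. For gamma with b = 1.5, the addition is 0.16 × 0.98² = 0.154.
- Change scores: 0.8 × 0.36 + 0.16 × δ² at correlation 0.5. The imputed zeros remove some variance, which partly offsets the lost signal.

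Simulation (20,000 trials per scenario, 22 per arm, correlation 0.5):

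| Assumed baseline | Completers, post or change | LOCF, post values | LOCF, change |
|---|---|---|---|
| 1.88 | 0.77 | 0.64-0.65 | 0.75 |
| 1.5 | 0.77 | 0.58 | 0.66-0.67 |
| 1.2 | 0.77 | 0.52 | 0.58 |

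Over correlations 0.3 to 0.7, LOCF on post values gives 0.51-0.65. On change, completers have about 0.61 and LOCF 0.48-0.60 at correlation 0.3. At 0.7 the figures are about 0.94 and 0.70-0.92.

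For post values, the loss of signal alone would require 17.6/0.64 = 27.5, or 28 analysed per group, to restore 80% by the plan's formula.

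**4. No true effect.** With equal 20% missingness the type I error stays at 5%. If missingness is unequal and all arms gain g, the bias in active minus sham is −(m_active − m_sham) × g. For assumed values of 10% sham and 30% in both active arms:

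| Common gain g | Bias | Type I error (correlation 0.4-0.8, post or change) |
|---|---|---|
| 0.1 | −0.02 | about 5% |
| 0.3 | −0.06 | 6-9% |
| 0.5 | −0.10 | 7-13% |

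The completer analysis stays at about 5% throughout.

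**5. True effect, unequal missingness, b = 1.5.**
- Sham 10%, gamma 30%: (0.7 × 2.48 + 0.3 × 1.5) − (0.9 × 1.88 + 0.1 × 1.5) = 2.186 − 1.842 = 0.34.
- Sham 30%, gamma 10%: 2.382 − 1.766 = 0.62.

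The true value is 0.60 in both cases, so the direction of the error depends on which arm loses more patients.

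**The case against.** **Not every dropout is affected.** A reader might infer that all of the planned 20% will be scored as zero change. The documents do not support that. The dropout criteria concern stopping the intervention, and the data section provides for continued collection afterwards. Only patients without the post-treatment 1-back are carried forward, and 20% is a planning allowance. This stands, and it limits the claim.

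**The power loss may be small.** The sample size section describes its means as mean differences, which points to change scores, although it then uses post-treatment values. On change, if sham does not improve at all (baseline 1.88), the loss is only about 2 points. This also stands. The documents leave open which score is tested, so both ranges are given. The pilot means come from nine patients.

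**False positives are not inevitable.** Type I error rises only if missingness is unequal and there is also a sizeable common gain. All arms are needled in the same way, and the needle-related events listed can occur under sham too. No figure in the protocol supports a 10% versus 30% split; it is an illustration.

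**The conflict in the text is narrow.** One might read the dropout criteria as contradicting the promise of further data collection, but stopping treatment and continuing assessment are compatible. The real tension is between terminating unblinded patients from the trial and the intention-to-treat and data-collection statements. Unblinding is reserved for critical emergencies and existing data are retrieved, so few patients should be involved.

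**A SAP could add detail.** It could, but the protocol names a rule and no alternative. This is a method fixed badly, not a gap left to another document.

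**Conclusion.** The point holds for patients without the post-treatment assessment: their imputed change is zero whatever is assumed about baseline, correlation or gain. With equal 20% missingness unrelated to outcome, the gamma-sham difference shrinks by a fifth and type I error stays at 5%, so the error is conservative. The power cost runs from about 2 points (change scores, no sham gain) to about 25 points (post values, baseline 1.2). In these scenarios, filling in the missing patients this way does worse than leaving them out. Bias in either direction and type I error above 5% are conditional on unequal missingness together with general improvement. The attenuation follows from the protocol's own numbers. The power and type I figures rest on the stated assumptions and should be read as ranges.

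**What to change.** 1. In the efficacy subsection, replace LOCF for the primary analysis with a baseline-adjusted analysis of all randomised patients that is valid under missing at random. Either a baseline/post mixed model with baseline means constrained equal across arms, or ANCOVA with multiple imputation using arm, baseline d' and centre, would serve.
2. Keep baseline carried forward as a sensitivity analysis, beside a delta-adjusted analysis that shifts the imputed values to see when the conclusion changes.
3. Reconcile the Blinding section's termination of unblinded patients with the intention-to-treat analysis and the data-collection promise. State that the already planned post-treatment assessment is sought for every randomised patient and analysed as randomised. This concerns outcome collection only, not whether treatment continues.

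The cost is a change of wording, modest extra analysis, and the effort of bringing back patients who stop early for an assessment already in the schedule. The drawback is reliance on missing at random, which the delta-adjusted analysis is there to probe.
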